### Data entry and management of data files

All data are entered into computerized database with the SAS software, V.9.3 (SAS Institute, Cary, North Carolina, USA). Values that are out of range or represent errors of faulty logic are avoided by double check. All participants’ data and patient health information will be confidential and protected during and after the trial. A code will be used to identify study participants, which will not be given to anyone outside of the study staff unless required by law. All paper records are stored in an area with two locked doors and/or drawers. Only the study staff will have access to the locks. All computerized records are password protected available only to the study team. We will use a data monitoring committee to provide oversight on integrity of the collected data.

### Ethics approval

All participants will be asked to sign the approved informed consent form prior to participation in the study. The study protocol (protocol version 2.0, issue date: 5 July 2021) was approved by the Ethics Committee of the Zhongda Hospital and Jinling Hospital under the number 2021ZDSYLL169-P01. The trial is conducted in keeping with Good Clinical Practice Guidelines, the principles outlined in the Declaration of Helsinki, and applicable local laws and regulations. The trial is registered at www.chictr.org.cn under the identification number ChiCTR2100049834. In the study, significant protocol modifications will be completed by the project applicants and primary investigators and resubmitted to the Ethics Committee for final review. After revising the program, there are researcher trains. If participants are involved, we will re-sign informed consent. We will perform audits to ensure that study protocol is followed every three months. Project management group meeting will be conducted both weekly and monthly. Weekly meeting will be held every Friday. Monthly meeting will be conducted at the last day of every month. The project management group will audit information on the research. The ethics committee will meet every 6 months.

### Dissemination

The final clinical report will be the basis for the study to be published in a medical journal and presented at national or international conferences. A person chosen by the lead investigators will jointly publish a formal report or publication of the study’s data. A report of the results of this study will be sent to the guardians of participants by mail. To ensure the scientific dissemination and transparency, de-identified data required to replicate our study can be supplied upon request with data usage agreements.

### Statistical methods

Outcomes will be analyzed by intention-to-treat and per-protocol. A low attrition rate is expected, since the interventions are of short duration and minimal risk. Missing data will be considered as missing. Data imputation will not be employed. Normally distributed data will be presented as means and standard deviation. Non-normally distributed data will be displayed as median and interquartile range. The significance of the differences between two groups will be tested by chi-squared test for categorical variables and t test for measurement data. Results with a *P* value lower than 0.05 for alpha error will be considered statistically significant. Statistical analyses will be performed using the SPSS 26.0 software (SPSS Inc., Chicago, IL, USA). We will do an interim analysis when the number of patients reaches half that.

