**Methods/design:**

The trial is a 3-month, multicentric, prospective, randomized controlled clinical study. Patients (i.e., adults with left ventricular ejection fraction ≤ 40%, Apnoea–Hypopnoea Index ≥ 15) will be randomized to receive optimized heart failure therapy plus a standard dose of dapagliflozin, while the control group will receive only optimized heart failure therapy. Patients will be evaluated before and after 3 months (nocturnal ventilatory polygraphy, echocardiography, laboratory testing, and quality-of-life and SDB questionnaires). The primary outcome is the change in the Apnoea–Hypopnoea Index, before and after 3 months of treatment.

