### Sample size

The sample size calculation for this trial was performed using the PASS 11.0 program [25]. The primary end point of the main study was the decreasing value of Apnoea–Hypopnoea Index (△AHI). Based on existing data, a 8 ± 6 events/h change in AHI events/h between the control and therapy groups was considered clinically relevant (assuming that AHI would not change in the control group) [26–28]. Based on a power of 90% and an alpha value of 5%, it was calculated that a sample size of 30 patients (considering the 20% sample loss rate) would be sufficient to detect a difference in the effect size of at least 10%. Data monitors from the two centers will supervise the study process at a fixed period.

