### Outcomes

#### Primary outcome

The primary endpoint of the trial is the AHI change determined by nocturnal polygraphy, before and after 3 months of treatment with dapagliflozin. The 2012 American Academy of Sleep Medicine recommendations are used to characterize apnea and hypopnea events, the phenotype, whether central, obstructive, or mixed.

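### The AHI change is compared by an unadjusted t test; adjusting for the baseline AHI already collected would be more precise, and the outcomes should be worded as dapagliflozin versus control

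*Protocol article*

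**What the plan says.** - **Test.** Statistical methods names one method for all continuous outcomes: "The significance of the differences between two groups will be tested by chi-squared test for categorical variables and t test for measurement data". It names no covariate.
- **Primary endpoint.** The Primary outcome section defines it as "the AHI change determined by nocturnal polygraphy, before and after 3 months of treatment with dapagliflozin". The Sample size section calls it the fall in AHI (△AHI), and the abstract words it without naming the drug: "The primary outcome is the change in the Apnoea–Hypopnoea Index, before and after 3 months of treatment". Most items under Secondary outcomes are also phrased as before and after dapagliflozin.
- **Effect assumed.** Under Sample size, "a 8 ± 6 events/h change in AHI events/h between the control and therapy groups was considered clinically relevant". That figure takes control-arm AHI to stay constant.
- **Data and allocation.** Table 2 schedules AHI at screening and at the day-84 visit. The Randomization process section adopts simple 1:1 randomisation and states no stratification.
- **Non-normal data.** Statistical methods adds: "Non-normally distributed data will be displayed as median and interquartile range". It names no other test or scale for such data.

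**The concern.** Baseline AHI is measured in every patient and can be expected to predict day-84 AHI. A t test on the change uses it in a fixed way: it subtracts the whole baseline value, whatever the true relation between the two visits. When the correlation is below 1 this over-corrects. The change is then negatively correlated with baseline, so an arm that starts higher by chance tends to show a larger fall. Simple randomisation of about 30 patients does nothing to limit such imbalance. ANCOVA estimates the slope instead, which removes that shift and reduces the residual variance.

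The outcome wording adds a smaller problem. Control patients receive no dapagliflozin, so an endpoint defined as change before and after dapagliflozin, read literally, exists in one arm only.

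At stake are some precision in a small trial, an estimate that carries part of any baseline imbalance, and an endpoint definition that does not state the contrast being tested.

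**Working it through.** **Inputs from the protocol (Sample size, Randomization process).** Difference 8 events/h; SD 6, read as the SD of the change; zero change in controls; 90% power; alpha 5%, taken as two-sided; 20% loss; 1:1 allocation; 30 patients in total.

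**Assumed, because the documents do not give it.** The correlation rho between baseline and day-84 AHI, taken as 0.5 to 0.9, with equal variances at the two visits.

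**1. The plan's own figure.** n per arm = 2 × [6 × (1.960 + 1.282) / 8]² = 11.82, rounded up to 12. Two arms give 24, and 24 / 0.80 = 30. The stated 30 reproduces, so the trial is sized for an unadjusted between-arm comparison of change.

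**2. Power of the planned test.** With 12 evaluable per arm, the noncentrality is 8 / (6 × √(2/12)) = 3.27 on 22 degrees of freedom. The noncentral t gives 87.7%, slightly under the stated 90%, because the sample size follows the normal approximation.

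**3. Chance imbalance.** The SE of the baseline difference is √(2/12) = 0.408 SD. P(|difference| > 0.5 SD) = 2 × [1 − Φ(0.5/0.408)] = 0.22.

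**4. What an imbalance does to the change score.** The SD at one visit is 6/√(2(1 − rho)). The expected shift in the change-score difference is 0.5 × that SD × (1 − rho), which equals 0.5 × 6 × √((1 − rho)/2).

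| rho | SD at one visit | shift from a 0.5 SD imbalance (events/h) |
|---|---|---|
| 0.5 | 6.0 | 1.5 |
| 0.7 | 7.7 | 1.2 |
| 0.8 | 9.5 | 0.9 |
| 0.9 | 13.4 | 0.7 |

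**5. Precision of ANCOVA.** Its residual variance is (1 + rho)/2 times the change-score variance, a cut of 25%, 15%, 10% and 5% at the four values. Putting 6 × √((1 + rho)/2) into the noncentral t gives 95%, 92%, 91% and 89%. These are upper values, since they ignore the cost of estimating the slope. Simulation of the fitted model (12 per arm, difference 8, change SD 6) gives the realistic figures:

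| rho | t test on change | ANCOVA, baseline only | ANCOVA, baseline and centre |
|---|---|---|---|
| 0.5 | 87.7% | about 94% | about 93% |
| 0.7 | 87.7% | about 91% | about 89% |
| 0.8 | 87.7% | about 89% | about 87% |
| 0.9 | 87.7% | about 88% | about 86% |

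The last column assumes two equally likely centres with no true centre effect. The centre term then costs 1 to 2 points, and at rho of 0.8 or above it removes the gain.

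**The case against.** A t test on change is a legitimate analysis. Over randomisations it is unbiased with the correct type I error, and it matches the basis of the sample size. Covariates are also often left to an analysis plan, which is not shown here. The first part stands, and it makes this a matter of precision rather than validity. The second has less force, because the protocol is not silent: it names the t test for all measurement data.

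Four stronger readings are tempting, and the documents do not support them.

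- *The plan discards baseline AHI.* It does not. The endpoint is a change score, so baseline is subtracted for every patient.
- *The between-arm question is undetermined.* Study design calls this a randomised controlled superiority trial, Sample size states a difference between control and therapy groups, and Statistical methods tests between two groups. Only the outcome wording is loose.
- *Regression to the mean after entry at AHI ≥ 15 biases the result.* Both arms enter under the same threshold and are randomised, so the expected fall is common to both and cancels. It would mislead only a within-arm before-after test, which Statistical methods does not plan.
- *Serious baseline imbalance is likely.* A probability of 22% is worth guarding against, but it is not likely.

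It is also fair to object that the gain rests on an unknown correlation. At rho 0.9 there is practically none.

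**Conclusion.** The point holds as a recommended improvement to a stated method. The planned test is valid and the sample size of 30 is not wrong on this account. Baseline-adjusted ANCOVA would add about 6 points of power at rho 0.5, 3 at 0.7, 1 at 0.8 and practically none at 0.9. It would also remove a shift of roughly 0.7 to 1.5 events/h for a 0.5 SD imbalance. These figures assume a difference of 8, a change SD of 6, equal variances at the two visits and 12 evaluable patients per arm.

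The before-and-after-dapagliflozin wording is a drafting fault, since the intended contrast can be recovered from other sections.

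A secondary point also holds. The plan foresees non-normal data but changes only how they are displayed. Markers such as NT-proBNP, CRP and IL-6 would be better analysed on the log scale if skewed. Any power gain there depends on the degree of skewness, which the documents do not give.

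**What to change.** 1. Word the primary outcome as the difference between dapagliflozin and control in AHI change from baseline to day 84, and reword the secondary outcomes the same way. Keep within-arm before-after values as description only.
2. Pre-specify ANCOVA of day-84 AHI on arm and baseline AHI, reporting the adjusted difference with its 95% CI.
3. Treat a centre term as optional. Randomisation is not stratified by centre, and the term costs 1 to 2 points of power if centre has no effect.
4. Analyse skewed markers on the log scale with log baseline as covariate.

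The cost is wording plus one residual degree of freedom (22 to 21 with 24 evaluable patients). Table 2 already schedules AHI and NT-proBNP, and inflammatory factors as a group, at screening and day 84, so no new measurement is needed. The sample size need not rise. The change should be fixed before any comparison by arm is run, including the interim analysis planned at half of recruitment.

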### Follow-up and duration of the study

There will be two visits at the clinical research center, one before (baseline) and one after (3 months follow-up) the dapagliflozin intervention. Data collection to assess efficacy of the intervention will be managed by research team members. An overview of the measures used at each of the four time points is illustrated in Table 2. For improving the compliableness of patients, the strategies are as follows: (1) adhere to the principle of voluntary participation and explain the benefits of this study to the participants and the importance of treatment and adherence to the treatment. Health education process could increase the related knowledge, change the behavior, and enhance the compliance of patient. (2) Written informed consent will be obtained from each patient before they begin the trial. All participants will fill in informed consents. (3) The treatment is free for participants, such as the relevant examination expenses and the telephone bill, traffic expenditures, and analgesic drugs incurred during the treatment and follow-up. (4) Record participants’ contact methods in detail, including mobile phone, WeChat, and e-mail for contact and follow-up.

**Table 2 Tab2:** Administration of study measures by assessment period

Research phase	Screening and randomization	Treatment period		
Interview	1	2	3	4
Research date	− 7–0	28 ± 2	56 ± 4	84 ± 6
Baseline information				
Informed consent	●			
General information	●			
History	●			
Physical examination	●	●	●	●
Treatment				
Inclusion/exclusion criteria	●			
Combined medication	●	●	●	●
Compliance		●	●	●
Completion of research				●
Inclusion/exclusion criteria				
PSG	●			
Echocardiography	●			
Security index				
Blood routine	●			●
Urine routine	●			●
Blood biochemical	●			●
Electrocardiogram	●			●
Adverse event assessment		●	●	●
Outcome				
AHI	●			●
Epworth Somnolence Scale (ESS)	●	●	●	●
Echocardiography	●			●
NT-proBNP	●			●
Quality of life as measured by the Minnesota Living with Heart Failure Questionnaire	●	●	●	●
EQ—5D—3L				
L_SpO2_	●			●
Inflammatory factors	●			●

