### Adverse events

The adverse events will be investigated by open questions, including general symptoms, and by specific questions regarding symptoms potentially related with the drugs used in the trial, as hypotension, frequent urination, urgent urination, fatigue, loss of appetite, nausea, vomiting, etc. The rate of adverse effects will be determined by comparing the frequency of adverse events in the experimental group and control group. The criteria for discontinuing the trial for an individual participant are as follows:Those who have serious adverse reactions in the study and are not suitable to continue to participate in the studyDuring the study period, the participants had other acute and severe diseases and needed to take emergency measures

(The reasons and time of withdrawal from the study will be recorded in detail. Participants who have exceeded 1/2 of the course of treatment will be included in the curative effect analysis.)

Researchers will do their best to prevent possible dangers caused by this study. If adverse events occur, the medical expert committee will identify whether they are related to drug treatment or research process. The project will provide treatment expenses and corresponding economic compensation for the damage related to the trial in accordance with the Criterions for the Quality Control of Clinical Trial of Drugs.

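### The two-visit sentence conflicts with Table 2, and the stated t test gives the day-28 and day-56 ESS and Minnesota scores no role

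*Protocol article*

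**What the plan says.** On visits, Follow-up and duration of the study states: "There will be two visits at the clinical research center, one before (baseline) and one after (3 months follow-up) the dapagliflozin intervention." Shortly afterwards the same section says: "An overview of the measures used at each of the four time points is illustrated in Table 2." Table 2 has four interview columns: day −7 to 0, then days 28, 56 and 84. ESS and the Minnesota questionnaire are marked in all four. So are physical examination and combined medication. Compliance and adverse events are marked at days 28, 56 and 84. AHI is marked only at baseline and day 84.

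On the contrast, Study design lists ESS and the Minnesota questionnaire in the pre-treatment evaluation and again in the final evaluation at 3 months. Secondary outcomes defines both only as before and after treatment.

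On analysis, Statistical methods plans intention-to-treat and per-protocol analyses, a "t test for measurement data", and missing values left missing: "Data imputation will not be employed." Adverse events adds a rule for withdrawn patients: "Participants who have exceeded 1/2 of the course of treatment will be included in the curative effect analysis."

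**The concern.** Two things do not fit together.

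First, the visit sentence and Table 2 lead to different data. A centre that works from the sentence would see nobody between baseline and 3 months. A centre that works from the table would hold two more contacts, each with a physical examination. With two centres, the interim scores, the compliance record and the chance to detect adverse events could differ by centre.

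Second, if the interim scores are collected, the stated analysis does nothing with them. A before/after t test needs a day-84 value, so a patient without one drops out even when day-28 or day-56 scores exist. The half-course rule wants some of those patients in the effect analysis, but the stated test has no value for them and imputation is barred. The intention-to-treat comparison of these two scores then becomes a completer comparison.

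**Working it through.** **1. The plan's own figure.** Sample size gives "a 8 ± 6 events/h change in AHI events/h between the control and therapy groups was considered clinically relevant", with 90% power, 5% alpha and 20% loss. Per arm: 2 × (1.960 + 1.282)² × 6² / 8² = 11.8, rounded up to 12. Total 24, and 24 / 0.8 = 30. The stated 30 reproduces (two-sided, normal approximation). It concerns AHI, which has no day-28 or day-56 value, so nothing below changes it.

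**2. Patients without day 84.** At the planned loss, 0.20 × 30 = 6 patients, about 3 per arm, leaving 12 per arm. Half of an 84-day course is day 42. A patient who leaves after day 42 but before the day-56 interview has baseline and day-28 scores. One who leaves after that interview has day 56 as well. Unless withdrawn patients are still assessed at day 84, which the article does not say, neither has a value for a day-84 t test.

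**3. Efficiency for ESS and Minnesota.** Assumptions, not in the documents: 15 per arm, 20% missing at day 84 and missing at random, equal variance at each visit (set to 1), and between-visit correlation r from 0.3 to 0.8. The correlation is either equal for all pairs (CS) or decays with distance (AR(1)). Let ρ be the baseline to day-84 correlation: r under CS, r³ under AR(1).

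- t test on change, completers: variance = 4(1 − ρ) / 12
- ANCOVA on baseline, completers: variance = 2(1 − ρ²) / 12
- Repeated-measures model: generalised least squares with known covariance, a shared baseline mean and all observed scores. In pattern (a), early leavers are split equally between baseline only, last seen at day 28 and last seen at day 56. In pattern (b), all are seen to day 56.

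Example, CS with r = 0.5: t test 4 × 0.5 / 12 = 0.1667; ANCOVA 2 × 0.75 / 12 = 0.1250; model (b) 0.1208. Baseline adjustment gives 0.1667 / 0.1250 = 1.33. The interim scores and early leavers add 0.1250 / 0.1208 = 1.034.

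| Structure, r | t test on change | ANCOVA | Model (a) | Model (b) | Model vs ANCOVA | Model vs t test |
|---|---|---|---|---|---|---|
| CS 0.3 | 0.2333 | 0.1517 | 0.1501 | 0.1490 | 1.010–1.018 | 1.55–1.57 |
| CS 0.5 | 0.1667 | 0.1250 | 0.1225 | 0.1208 | 1.021–1.034 | 1.36–1.38 |
| CS 0.7 | 0.1000 | 0.0850 | 0.0825 | 0.0809 | 1.031–1.050 | 1.21–1.24 |
| CS 0.8 | 0.0667 | 0.0600 | 0.0580 | 0.0567 | 1.035–1.058 | 1.15–1.18 |
| AR(1) 0.3 | 0.3243 | 0.1665 | 0.1653 | 0.1636 | 1.007–1.018 | 1.96–1.98 |
| AR(1) 0.5 | 0.2917 | 0.1641 | 0.1605 | 0.1562 | 1.022–1.050 | 1.82–1.87 |
| AR(1) 0.7 | 0.2190 | 0.1471 | 0.1409 | 0.1346 | 1.043–1.092 | 1.55–1.63 |
| AR(1) 0.8 | 0.1627 | 0.1230 | 0.1165 | 0.1104 | 1.055–1.114 | 1.40–1.47 |

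The ANCOVA gain over the t test on change is 2 / (1 + ρ). It exceeds the further gain from the interim scores in every row.

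**The case against.** The two-visit sentence is limited to visits at the research center, Table 2 calls its columns interviews, and the section records telephone, WeChat and e-mail for follow-up. Questionnaires, compliance and adverse-event questions can be handled remotely. This stands for those items, but not for the physical examination marked at days 28 and 56.

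A before/after t test is a valid analysis of a before/after outcome, and Statistical methods expects low attrition, so the 20% may overstate the loss. This also stands: the issue is efficiency and consistency, not validity in a complete data set. A repeated-measures analysis may sit in an analysis plan that is not shown. However, the article does not leave the method open: it names the test and bars imputation. The visit schedule is a protocol matter in any case.

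Several stronger readings are not supported:

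- A reader might infer that the text allows only two contacts, so the interim scores are never collected. The same section refers to four time points.
- A reader might say that a t test cannot use the interim scores. It can be run at each time point; it cannot combine them or carry early leavers' information to day 84.
- A reader might see a free choice among three time points. Study design and Secondary outcomes point to baseline versus 3 months.
- A reader might conclude that everyone lost before day 84 is to be discarded. The half-course rule says otherwise, though no method carries it out.
- A reader might credit the interim scores with a variance reduction of 5%, 10% or 13% (0.2r² for r = 0.5, 0.7, 0.8). That compares with a raw completer mean that ignores baseline, and assumes every early leaver has an interim score. If only half do, the reduction is 0.111r²: about 3%, 5% and 7%.

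**Conclusion.** The point holds as a modest one. The visit sentence and Table 2 disagree, and which one is followed decides what each centre collects. For ESS and Minnesota, the stated t test does not adjust for baseline, leaves the day-28 and day-56 scores without a role, and has no value for half-course patients who lack day 84.

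Under the assumptions above, a baseline-adjusted repeated-measures model is 1.15 to 1.98 times as efficient as a t test on change. Most of that is baseline adjustment; the interim scores and early leavers contribute about 1% to 11% beyond a completer ANCOVA. These figures treat the covariance as known, so they are somewhat favourable to the model in a trial of 30. Only secondary outcomes are affected. It would be wrong to infer that the primary result or the sample size is in doubt.

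**What to change.** 1. Bring the two-visit sentence into agreement with Table 2, and state for days 28 and 56 whether each item is done in person or remotely, so that both centres work to one schedule.
2. Analyse ESS and the Minnesota score each with one mixed model for repeated measures: arm, visit, arm by visit, baseline score and centre. Name the day-84 difference as the target and report days 28 and 56 descriptively. The model uses all observed scores under a missing-at-random assumption, without imputation.
3. State how the half-course rule applies: to which outcomes and analysis sets, and which observed values represent a patient without day 84.

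The cost is wording in the protocol and analysis plan. No patients or assessments are added beyond Table 2, and SPSS, the named package, fits the model. The downside is a slightly more complex analysis in a small sample: an unstructured covariance over three post-baseline visits has 3 variances and 3 covariances to estimate from at most 30 patients.

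### An interim analysis at half the patients has no stated purpose or boundary beside a lone P < 0.05 rule; two efficacy tests at 0.05 would raise type I error to about 8.3–8.5%

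*Protocol article*

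**What the plan says.** All of this is in the protocol article.

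- **Statistical methods, interim look.** "We will do an interim analysis when the number of patients reaches half that". This is the only sentence on the interim analysis. It gives no purpose, endpoint, threshold or consequence.
- **Statistical methods, significance.** The one rule is that a P "value lower than 0.05 for alpha error will be considered statistically significant". It is worded for results in general and is not tied to the final analysis.
- **Statistical methods, test.** Group differences in continuous outcomes are assessed by "t test for measurement data".
- **Primary outcome.** "The primary endpoint of the trial is the AHI change determined by nocturnal polygraphy", over 3 months. Table 2 schedules AHI at baseline and at day 84 only.
- **Sample size.** The calculation is "Based on a power of 90% and an alpha value of 5" per cent. It takes "a 8 ± 6 events/h change in AHI events/h between the control and therapy groups was considered clinically relevant" and concludes that "a sample size of 30 patients (considering the 20% sample loss rate) would be sufficient". No interim look is mentioned.
- **Data entry and management of data files.** A data monitoring committee is named, but its stated task concerns only the integrity of the collected data.

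**The concern.** A 5% alpha in the sample size calculation means a 5% chance of a false claim over the whole trial. A second efficacy test at the same 0.05 threshold is a second chance of a false claim, so the overall error exceeds 5% unless the thresholds are tightened. Here an interim analysis is promised in the same paragraph as an unqualified 0.05 rule. Nothing elsewhere in the article keeps the two apart: no passage limits the look to safety, and none gives a stopping boundary. A superiority trial of 30 patients could therefore be called positive at its midpoint without its stated error rate being protected. The Discussion concedes that there is neither double blinding nor placebo, and no passage limits who sees interim results, so the purpose of the look is worth fixing in advance.

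**Working it through.** **Inputs from the article.** Difference 8 and SD 6 events/h, alpha 5%, power 90%, 20% loss and 30 patients (Sample size); 1:1 allocation (Randomization process); t test and P < 0.05 (Statistical methods).

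**Assumptions, because the article does not state them.** The test is two-sided. The 30 patients are the total for both arms. The interim holds half of the final AHI information. The interim tests AHI change for efficacy, and success can be claimed at either look.

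**Step 1: reproduce the sample size.** With the normal-approximation formula:

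n per arm = 2 × (1.960 + 1.282)² × 6² / 8² = 2 × 10.51 × 0.5625 = 11.8, rounded up to 12.

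Allowing for loss: 12 / (1 − 0.20) = 15 per arm, 30 in total. This matches the stated figure exactly. A one-sided test would need only 10 per arm before loss, so the two-sided reading fits. The calculation is for one test at 5%. By the exact t test, 12 evaluable patients per arm give 87.7% power, which is the baseline for costing the fix.

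**Step 2: two looks at 0.05.** With half the information at the interim, the two test statistics have correlation √0.5 = 0.707 under the null. The overall error is

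P(|Z₁| > 1.96 or |Z₂| > 1.96) = 8.31%.

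Simulated t tests at the trial's own sizes (2,000,000 null trials each) give:

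| Interim, then final | Overall type I error |
|---|---|
| 8+7, then 15+15 (no loss) | 8.45% |
| 6+6, then 12+12 (20% loss) | 8.48% |

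Testing only at the end gives 5.0%.

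**Step 3: vary the assumptions.** If half means half enrolled, some of those patients will not yet have a day-84 AHI, and the information fraction is below 0.5. By normal theory:

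| Information fraction at interim | Overall type I error |
|---|---|
| 0.5 | 8.3% |
| 0.4 | 8.6% |
| 0.3 | 8.9% |
| 0.2 | 9.2% |

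A one-sided 5% test at both looks, at fraction 0.5, gives 8.0%.

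**Step 4: check a boundary.** O'Brien-Fleming thresholds of P < 0.0052 at half (|z| > 2.79) and P < 0.048 at the end (|z| > 1.98) give 5.00% by normal theory and 5.1% by t tests at 6 then 12 per arm. At a true difference of 8 with SD 6, power is about 87.4%, against 87.7% for a single final test at 0.05.

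**The case against.** **The purpose of the look is unknown.** A reader might infer that the trial's type I error simply is 8.3–8.5%. The article does not support that. It never says that the interim compares AHI between arms, uses 0.05, or can end in a claim of success. The discontinuation criteria under Adverse events concern individual participants only. If the interim carries no efficacy claim, the error is 5.0%. This stands, and the figure has to be stated as conditional.

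**The detail may lie elsewhere.** The article condenses protocol version 2.0, and a statistical analysis plan may exist. Boundaries and the definition of half are commonly left to those documents, so their absence alone would be no finding. What remains is narrower. The article is not silent: it commits to an interim analysis and, beside it, fixes a general 0.05 rule that as worded also covers interim results. Together these do not protect the 5% alpha used for the sample size.

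**Overestimation at the interim.** A reader might add that a significant result on about six patients per arm would exaggerate the effect. It would: at a true difference of 4 events/h, significant interim results favouring dapagliflozin average about 8.6 at the 0.05 threshold, and at a true difference of 8 they average 10.2. But the O'Brien-Fleming boundary does not cure this. Its crossings average 10.3 and 12.0 respectively; they are only rarer (about 3% against 18% of trials at a true difference of 4). The exaggeration comes from small numbers and selection on significance, so it is no argument for this point. Six per arm is itself an assumption, since the article expects low attrition and uses simple randomization.

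**Conclusion.** The point holds in conditional form. The article plans an interim analysis without a purpose or boundary, its only significance rule is P < 0.05, and its sample size is that of a single 5% test. If AHI change is tested at two-sided 0.05 at both looks and success can be claimed at either, the type I error is about 8.3–8.5% instead of 5%. That range assumes half of the AHI information at the interim. It rises to 8.6–9.2% at information fractions of 0.4 down to 0.2, which is the direction to expect if half is counted at enrolment. The arithmetic is secure. Whether the inflation would occur depends on what the interim is for, which the article leaves open.

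**What to change.** Settle this in writing before any interim data are seen, because a rule added afterwards would not be credible. Either of two statements is enough:

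1. The interim covers safety, data quality and the pooled SD only, with no between-arm AHI comparison, and 0.05 is kept for the single final test. This costs no alpha and no power.
2. The interim tests efficacy against a prespecified boundary that holds overall alpha at 5%. One example is O'Brien-Fleming, with two-sided P < 0.0052 at half and P < 0.048 at the end. Other boundaries that hold 5% would also serve.

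Under the second option, count half in patients with a day-84 AHI rather than patients enrolled, so that the information fraction matches the boundary.

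The change takes a sentence or two. Under O'Brien-Fleming, power falls from about 87.7% to 87.4% at 12 evaluable patients per arm, well under one percentage point. If protocol version 2.0 or an analysis plan already contains such a rule, it is enough to cite it.
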